**Input parameters**			
	Effect size *f*(*V*)	0.2318206	
	α err prob	.05	
	Power (1−β err prob)	0.9	
	Number of groups	3	
	Number of measurements	4	
	Nonsphericity correction ε	1	
**Output** **parameters**			
	Noncentrality parameter λ	17.5732385	
	Critical *F*	2.1078920	
	Numerator df	6.0000000	
	Denominator df	972	
	Total sample size	327 (109 per group)	
	Actual power	0.9007901	

## Results

The medical ethics committee of the UMCG approved the study in April 2022. This study began recruiting its participants in June 2022 and upon submission had recruited and collected data from 5 participants. Preliminary data analysis will commence once enough data have been collected to reach 0.8 power. Data collection is expected to be finished in 2026. The study results will be available within 1 year of completed data collection and shared in local, national, and international meetings within the medical, scientific, hospital administrative, and medical professional communities as well as the general public.

## Discussion

### Principal Findings

Previous studies have shown that postoperative pain management can be supplemented with music intervention. Yet, little is known about the benefits of live versus recorded music, or what physiological mechanisms may be mitigating pain perception as a response to listening to music. This NCT will compare the MiMiC live music intervention with listening to recorded music and care-as-usual. The primary objective is to see whether pain VAS ratings differ across the 3 conditions, and the secondary objective is to see whether postoperative neuroinflammation is reduced as a response to listening to music.

The strength of this study is the inclusion of preoperative assessments to establish some baseline characteristics of patients. First, the preoperative musical background questionnaire (selected items from [30]) assesses the estimated weekly hours of music listening as well as listening preferences for musical genre and whether or how the participant is musically trained. This provides us the opportunity to analyze how the extent of musical exposure may affect the primary outcome (pain VAS) of the intervention; depending on the strength of these findings, we may be able to even help inform future music interventions according to preoperative musical habits. Second, the preoperative cognitive assessment (6CIT) [28] serves as an important baseline for several secondary outcomes that may help to account for variability among the 3 intervention arms that otherwise might be attributed to the treatment. Specifically, the 6CIT will inform the interpretation of the postoperative cognitive status, and it may predict alpha power in EEG recording [22] that in turn may be linked to delirium [23,24]. If this proves to be the case, the preoperative cognitive status might be investigated in the future as a method to inform more at-risk patients who could especially benefit from supplementary nonpharmacological interventions [41] such as live or recorded music [42].

### Limitations

While postoperative pain is common to most patients undergoing surgical intervention in hospital, other characteristics surrounding the surgery (eg, type of surgery, duration of surgery, and underlying medical need for surgery) are widely varied across patients. Thus, a limitation of the study is that we will have a heterogeneous patient group. Considering that reduced pain VAS among patients experiencing MiMiC live music intervention compared to care-as-usual was previously a robust finding in a heterogeneous patient group [1], we do not consider our primary outcome to be affected by this heterogeneity. However, secondary outcomes related to finding neurophysiological markers of inflammation, and whether they are influenced by a music intervention, might be greatly affected by this heterogeneity. Moreover, the short duration of the intervention may further limit proper interpretation of inflammatory biomarkers, since previous studies have found neuroinflammatory biomarkers readings to be informative to overall interpretation 5 to 14 days after a medical event [43,44]. We may therefore form posthoc groups with similar surgery types when evaluating secondary outcomes, which could inform future hypotheses for further, longer term clinical research on music interventions and postsurgical neuroinflammation.

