## Methods

### Study Design

The study will take place at the University Medical Center Groningen (UMCG), which has already hosted the Meaningful Music in Healthcare (MiMiC) live intervention [25]. The intervention study follows an on-off nonrandomized controlled trial (NCT) design [26]. The NCT is necessary for this particular intervention in practice because the live music intervention cannot easily be randomized to skip patients in the same ward without them hearing the music or seeing the musicians as they play for other patients and nurses.

In this NCT design, treatments and data collection will be conducted in 15 blocks over the course of 4 years. According to the 29-day treatment block, the three 5-day treatments (live music intervention, recorded music active control intervention, and standard care control) will be offered with a 7-day washout between treatments. The washout will minimize the number of participants whose hospital stay overlaps with another treatment. Based on the previous research (UMCG research register 201600541), we expect approximately 8 full data sets per 5-day treatment block.

Note that while the intended outcome of the music intervention is therapeutic (eg, experiencing reduced pain), the music intervention is conducted by conservatory-trained music practitioners but not by music therapists. Music therapists are licensed therapists who have a degree in music therapy including clinical training. The music practitioners in this study are primarily professional musicians who have taken 1 music-conservatory course and several internships to train them for clinical settings but they are not therapists.

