### Inclusion Criteria

In order to be eligible to participate in this study, a subject must meet all of the following criteria: (1) 18 years or older, (2) postsurgery hospitalization (all surgery types), (3) elective surgery, (4) able to hear music, (5) able to give informed consent, and (6) able to communicate.

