### Treatment Allocation

This study will take the form of an on-off NCT [26]. An on-off NCT takes into account real-world setting limitations of certain intervention types and allocates participant inclusion by alternation. The main reason for this is that MiMiC is a well-researched intervention, whose practical implementation is not suited for randomly selected participants to not participate. On the one hand, musicians will visit the nurses’ station and play music in various rooms around the ward; thus, it is not possible to prevent participants who may be allocated non-MiMiC treatment from hearing the live music. On the other hand, a central tenet of the MiMiC intervention is inclusion and participation, thus “rejecting” patients who would want to participate in music they hear on the ward, on the basis of trial group allocation, goes against the spirit of the intervention.

In contrast, the NCT relies on the randomness of who is scheduled for surgery during a given intervention week but does not exclude any patient from the activity being conducted (listening to live or recorded music). Therefore, the treatment schedule (live music intervention, recorded music active control, and standard care control) will be predetermined months in advance, and the patients included will be offered whichever treatment is occurring during their hospital stay. The patients will, however, be asked for their consent before they are informed which treatment will be offered during their surgery recovery. This will attempt to prevent patients who are initially biased for inclusion based on their affinity to music or not.

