### Other Study Parameters

Posthoc analyses will be conducted to inform recommendations for participant grouping in future studies. Continuous baseline parameters (eg, age; see “Other Parameters” section for a full list) will be treated as covariates in an ANOVA in order to see whether the addition of these elements improves the model for each outcome. Similarly, categorical baseline parameters (eg, type of surgery) will be coded and entered as an additional factor (two-way RM ANOVA: treatment×baseline×time point) to see whether the additional factor can explain more variance than in the primary analysis model.

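### The primary test carries no case-mix adjustment although arms are not randomised, and the claim that heterogeneity leaves the primary outcome untouched does not follow

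*Protocol article*

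**What the plan says.** **Allocation.** Treatment Allocation describes a design that "allocates participant inclusion by alternation" and states that "the NCT relies on the randomness of who is scheduled for surgery during a given intervention week". The Inclusion Criteria admit every type of elective surgery. Study Design gives the scale: "treatments and data collection will be conducted in 15 blocks over the course of 4 years", each block holding one 5-day period per treatment, and "we expect approximately 8 full data sets per 5-day treatment block".

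**Primary model.** Primary Study Parameters (Statistical Analysis) specifies a repeated-measures ANOVA of the pain VAS with group and time point as the only factors. The test of interest is their interaction over four ratings, the first taken before treatment. If residuals are not normal, a Kruskal-Wallis test replaces it.

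**Covariates.** The list of other study parameters under Study Parameters and End Points includes comorbidity, surgery characteristics, postoperative day and age. Their analytic use is set out in Other Study Parameters under Statistical Analysis: "Posthoc analyses will be conducted to inform recommendations for participant grouping in future studies". There, continuous parameters are tried as covariates and categorical ones as an extra factor, to see whether the model improves.

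**Reassurance.** Limitations concedes that surgery type, duration and medical need vary widely. It then says "we do not consider our primary outcome to be affected by this heterogeneity", pointing to a cited study in which live music did better than usual care in a heterogeneous group.

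**The concern.** Without randomisation, comparability of the arms rests on the surgical lists being alike from one treatment week to another. The plan collects the variables that could correct for a difference but gives them no part in the primary analysis. Models judged by whether they explain more variance, and run to advise later studies, do not control confounding.

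The reassurance answers a different question. A positive result in a mixed population bears on whether an effect can be seen despite heterogeneity. It does not show that three non-randomised arms in a new study have the same mix. As described, it also covers live music against usual care only, whereas the Introduction names live against recorded music as the primary comparison.

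At stake is whether a significant interaction can be read as an effect of music.

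**Working it through.** **1. The plan's own figure.** f = √(0.051/0.949) = 0.2318. With λ = f² × N = 0.2318206² × 327 = 17.573, numerator df (3−1)(4−1) = 6 and denominator df (327−3)(4−1) = 972, critical F is 2.108 and power 0.9008. Table 3 reproduces exactly, and it is for the unadjusted model.

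**2. Inputs for the bias check.**
- From the document: 15 weeks per arm × 8 patients = 120 per arm, 360 in all; four ratings; α = .05. Error df are (360−3) × 3 = 1071.
- Assumed, because the document gives nothing on them: no true music effect; one binary case-mix factor (major against minor surgery); a course difference between the two classes that grows in equal steps over the four ratings to b residual SD at the 6-hour rating, with b from 1 to 2.

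**3. Level differences.** The interaction test uses each rating minus the patient's own mean, so a constant shift drops out. Simulated with a 1.5-point shift and prevalence 30/50/70% across arms, type I error of the interaction test stays at .05. A one-way comparison of the arms' mean pain levels on the same data rejects in .51. The Kruskal-Wallis fallback has no interaction term. If it were run on pain levels it would be exposed in that way; the .51 comes from an F test on patient means, used here as a stand-in.

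**4. Course differences, systematic imbalance.** Centred, the steps 0, 1/3, 2/3, 1 become −1/2, −1/6, 1/6, 1/2, with sum of squares 0.556. If the outer arms lie d below and above the middle arm in prevalence, the spurious noncentrality is λ = 120 × 2d² × b² × 0.556. With b = 1:
- 40/50/60% (d = .1): λ = 1.33, rejection probability about .11. Simulations gave .105 to .115.
- 30/50/70% (d = .2): λ = 5.33, rejection probability about .36. Simulations gave .35 to .39.

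A different shape, in which the whole difference is present from the second rating on, gave .09 and .21 for 1.0 point with within-patient SD 1.5 (40/50/60% and 30/50/70%), and .45 for 1.5 points with 30/50/70%.

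**5. Course differences, random variation between weeks.** Mean share of major surgery 40%, b = 1 to 2, simulated in weeks of 8:

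| Weekly SD of the share | Unadjusted type I error |
|---|---|
| 0 (chance only) | about .05 |
| .15 | about .06-.08 |
| .2 | about .06-.11 |

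**6. Adjusted test.** With the factor crossed with time point in the model, type I error was .04 to .06 in every scenario.

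**The case against.** The strongest defence is that the planned test already removes much of the problem. It measures change from a pre-treatment rating, so stable differences in pain level cancel. Treatments alternate over 15 blocks, which limits drift, and patients consent before learning which treatment they will get. With purely chance variation in case mix, error stays near .05. The document shows no mechanism for systematic imbalance and no evidence that surgery type alters the within-day course of pain. All of this stands, and it makes the risk conditional. It does not rescue the sentence in Limitations, and the timing of disclosure does nothing about surgical case mix.

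Several stronger readings are tempting and are not supported:
- A reader might infer that any case-mix difference passes as a music effect. Level differences do not, in the planned interaction test.
- Principal Findings says a baseline measure "may help to account for variability among the 3 intervention arms that otherwise might be attributed to the treatment". This concerns the 6CIT and secondary outcomes, and is no admission about pain or surgical mix.
- One might think the covariate models ignore time. Other Study Parameters already crosses categorical parameters with time point; the issue is that these models are post hoc.
- The post hoc surgery groups in Limitations are for secondary outcomes only. Nor does that section offer its sentence as the reason for omitting covariates.
- Two arms of 120 at 40% prevalence differ by more than 10 percentage points in about 11% of comparisons by chance alone: the SD of the difference is √(2 × .4 × .6/120) = .063. Individual randomisation would give the same, so this is no cost of the design.
- Adjustment might raise power, but by an amount that depends on an assumed share of variance explained by covariate × time point. That is a side benefit; its absence is not an error in the plan.

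**Conclusion.** The point holds in conditional form. The text is clear: allocation is not randomised, the primary model is unadjusted, and the relevant covariates are collected but confined to post hoc use. The statement that heterogeneity does not affect the primary outcome does not follow from the evidence given for it.

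The size is uncertain. Bias in the planned test needs two things together: case mix that differs between arms, and case mix that changes the course of pain over the day. If the weekly lists differ only by chance, there is essentially no inflation. If they vary moderately from week to week, error rises to at most about .11 under the values tried. The large figures (.35 to .39, or .45 for the step-shaped course) require a systematic 30/50/70% imbalance, which the document gives no reason to expect. The prevalences, SDs and course differences are all assumptions. Because the correction is cheap and uses data already collected, it should be made.

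**What to change.** In Primary Study Parameters (Statistical Analysis):
- Make the primary model group × time point with surgery category or invasiveness, postoperative day at the first session, and age, each crossed with time point. Leave out the treatment × baseline × time point term of Other Study Parameters, which asks a different question.
- Keep the unadjusted model as a sensitivity analysis.
- Fix the surgery categories in writing before any comparison by arm.

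In Limitations, delete the sentence on the primary outcome. Alternatively, qualify it to say that level differences cancel in the interaction test, while differences in the course of pain are handled by adjustment.

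The cost is a short surgery classification and a few degrees of freedom. Each covariate column crossed with four time points uses 3 error df, so four columns (for example three surgery categories, postoperative day and age) use 12 of 1071. No new data are needed, and only 5 participants had been recruited when the article was submitted.

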### Conclusions

Upon completing this study, we will contribute a systematic comparison of the effects of live versus recorded music on postoperative pain. This study can ultimately inform policy makers as to the benefits to patient pain outcomes when incorporating live versus recorded music in postoperative recovery settings.

## Abbreviations

6CIT: 6-item cognitive assessment
CRP: C-reactive protein
DMBQ: Dutch Musical Background Questionnaire
DOSS: delirium observation screening scale
EEG: electroencephalogram
HR: heart rate
IL6: interleukin-6
MiMiC: Meaningful Music in Healthcare
NCT: nonrandomized controlled trial
NGAL: neutrophil gelatinase–associated lipocalin
POCD: postoperative cognitive decline
RM: repeated measures
TPSO: translocator protein
UMCG: University Medical Center Groningen
VAS: visual analog scale
